*Physical and social activity*: as a protective factor for mental health, social activity refers to daily interactions with different groups of people in the immediate social environment. It will be measured with the item: “With whom have you spend the majority of your day?” using alone, partner, friends, family, colleagues, and other as categories. Physical activity is monitored as a protective factor of mental health and will be measured with an item extracted from the International Physical Activity Questionnaire (IPAQ SA Short) (53). The item “Have you been physically active today?” uses four answer categories to assess low-, moderate- and high-intensity activities, and also no activity as an indicator for sedentary behavior. Appropriate examples for each category will be provided for instruction (e.g., low-intensity activity “walking at least 10 min a day”).

*Alcohol and drug use*: as a risk factor for psychopathology, daily reports of drinks consumed using the categories beer, wine, liquor, and other will be collected. From this, the number of standard drinks consumed per day will be calculated. Participants will be familiarized with the concept of a standard drink and the volumes of different beverages that are equivalent to a standard drink (54). The German definition of standard drinks will be used (men: 20 g alcohol, women: 10 g alcohol). Two measures of alcohol use will be constructed: days with any drinking and days with heavy drinking (defined by five drinks for men and four drinks in for women). For drug use, the daily occurrence and frequency of any illegal substance will be assessed.

*Impairment*: the individuals’ functioning in the context of social and occupational roles, which is assumed to be a central component of mental health will be monitored. We use a single-item scale from the PHQ-4 (55), which measures subjective impairment in work and household duties and in social relationship on the present day on a 4-point scale with the item: “How difficult have these problems made it for you to do your work, take care of things at home, or get along with other people?”

*Context*: contextual information on daily locations will be monitored as a risk or protective factor of mental health. For this purpose the item “Where were you the majority of the day?” will be used with the categories: at home, visiting friends or family, work or school, outbound, and other.

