*Differential effectiveness*: to examine person-level moderators of the intervention effect, a between-person factor is added to the MANOVA. This results in a three-way interaction (person factor × time × group). However, as only categorical person variables can be included in the MANOVA, multivariate multilevel models for fixed occasions will also be performed to allow for continuous variables as moderators (105). The between-person moderators to be included in the analysis of differential effectiveness include gender, age, and baseline distress severity (low, moderate, high).

Conditional effectiveness: to examine whether time-varying characteristics of the situation (e.g., days spent at work) or the individual (e.g., being physically active) might moderate the intervention effect, multivariate multilevel models will be extended with a continuous or categorical day-level variable. To estimate the pure within-person effect of the time-varying moderator, continuous day-level variables will be centered on the person-mean.

*Effect sizes*: Cohen’s *d* will be calculated as a measure of the effect size, where *d* = 0.8 or more is classified as a large effect, *d* = 0.5–0.8 is classified as a moderate effect, and *d* = 0.2–0.5 is classified as a small effect. According to Feingold (106), the raw score standard deviation of the outcome variable at baseline assessment will be used to compute Cohen’s *d*.

*Treatment response*: changes in mental health on an individual level will be examined with the widely used Reliable Change Index (RCI) by Jacobson and Truax (107). Participants with an RCI greater than 1.96 will be classified as “responders,” and those with an RCI below −1.96 will be classified as “deteriorated.” To assess the average number of persons who need to be treated to prevent one additional bad outcome, the number needed-to-treat (NNT) will be calculated. Additionally, the number-needed-to-harm (NNH) will be calculated, indicating the number of responders in the intervention group for one extra person to have a symptom deterioration. To set the benefits of the intervention in relation to its risk, the benefit-risk ratio will be calculated by dividing the NNT through the NNH (108).

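### Person-mean centring is prescribed for continuous day-level moderators only, yet both example moderators are categorical, so the stated within-person aim is not fully met for them (minor; secondary analysis)

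*Protocol article*

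**What the plan says.** The paragraph on conditional effectiveness (Statistical Analysis) asks whether "time-varying characteristics of the situation (e.g., days spent at work) or the individual (e.g., being physically active) might moderate the intervention effect". For this, "multivariate multilevel models will be extended with a continuous or categorical day-level variable". The purpose of centring is given without restriction to one type of variable: "To estimate the pure within-person effect of the time-varying moderator". The rule that follows is restricted: "continuous day-level variables will be centered on the person-mean".

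The Self-Monitoring section shows how the two examples are measured. Location, from which days at work are derived, is a nominal item that "will be used with the categories: at home, visiting friends or family, work or school, outbound, and other". Physical activity is one item that "uses four answer categories to assess low-, moderate- and high-intensity activities, and also no activity as an indicator for sedentary behavior". Neither is continuous.

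The only other relevant statement is a general remark, earlier in Statistical Analysis, that the models analyse within-person and between-person variance. It names no person-mean term and no centring of indicators.

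**The concern.** The rule is narrower than the aim it serves. A random intercept splits the variance of the outcome into two levels. It does not split the slope of a predictor that itself varies both within and between people. A work-day indicator entered as 0/1 carries two contrasts: this person's work days against the same person's other days, and people with many work days against people with few.

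The article separates differential effectiveness (person-level moderators) from conditional effectiveness (time-varying moderators). An uncentred product of group and indicator blurs that line. It can pick up whether the intervention works differently for people who have many such days, when the question is whether it works differently on such days.

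**Working it through.** **Inputs.** From the article: up to 28 daily reports per person (Adherence) and 62 people per arm (Sample Size Calculation). Daily data exist only in the supported-monitoring arm and the self-monitoring-only arm, because the passive control group does no self-monitoring. Not in the article, so assumed: ICC 0.2 to 0.6, the mean share of exposed days, and its spread between people. The plan states no figure on this point, so there is none to reproduce.

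**Formula.** Take a random-intercept model with total variance 1, T reports per person, mean share p, and between-person variance v of that share. The uncentred slope is (1 − w) × within slope + w × between slope, where

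- within variance of the indicator: Vw = (p(1 − p) − v)(T − 1)/T
- variance of the person means: Vb = v + (p(1 − p) − v)/T
- Iw = T·Vw/(1 − ICC)
- Ib = Vb/(ICC + (1 − ICC)/T)
- w = Ib/(Iw + Ib)

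**Worked case.** T = 28, ICC 0.4, share distributed Beta(2,2), so p = 0.5 and v = 0.05. Then Vw = 0.20 × 27/28 = 0.193 and Vb = 0.05 + 0.20/28 = 0.057. Iw = 28 × 0.193/0.6 = 9.0. Ib = 0.057/(0.4 + 0.6/28) = 0.136. So w = 0.136/9.136 = 1.5%.

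**Between-person weight w**

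| Spread of share | Reports | ICC 0.2 | ICC 0.4 | ICC 0.6 |
|---|---|---|---|---|
| Moderate, Beta(2,2), v = 0.05 | 28 | 3.6% | 1.5% | 0.7% |
| Moderate | 14 | 7.1% | 3.2% | 1.6% |
| Wide, Beta(0.6,0.6), v = 0.114 | 28 | 10.1% | 4.4% | 2.0% |
| Wide | 14 | 17.8% | 8.6% | 4.2% |

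A second set of assumptions (p = 0.4, v from 0.02 to 0.12, same ICC range) gives 0.3 to 12% with 28 reports and 0.8 to 20% with 14.

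**What this does to the moderation term.** Let W₀, W₁ be the within-person slopes and B₀, B₁ the between-person slopes in the two arms. If the spread of exposure is similar in both arms, w is common, and the difference between the arms' uncentred slopes is

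(W₁ − W₀) + w·[(B₁ − B₀) − (W₁ − W₀)].

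A between-person slope that is equal in both arms (B₁ = B₀) contributes nothing. The term is contaminated only when B₁ differs from B₀, that is, when the intervention effect varies with a person's share of such days. The main effect of the indicator has no such protection: its bias is w(B − W).

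**Simulation checks, two arms of 62.**

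- *Between-person slope of 1 SD per unit share, equal in both arms.* The uncentred interaction averaged between −0.005 and +0.004 SD. The 5% test rejected 4 to 7%, even with 14 reports and ICC 0.2.
- *Between-person interaction of 1 SD per unit share, no within-person moderation.* The 5% test rejected 6 to 8% with 28 reports and ICC 0.4, and 11 to 35% with 14 reports and ICC 0.2. With centring it rejected 4 to 6%.
- *Fitted mixed models, 28 reports, ICC 0.4, 60 runs.* The true within slope was −0.20; the between slope was −1.0, with a further −1.0 in the intervention arm; there was no within-person moderation. The uncentred model gave slope −0.212 and interaction −0.025. The centred model with person means gave −0.200 and −0.010. Monte Carlo standard errors were about 0.005 and 0.008. The formula gives w = 1.9% here, so the expected shifts are 0.019 × (−1.0 + 0.2) = −0.015 and 0.019 × (−1.0) = −0.019.

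**The case against.** The strongest reply has four parts.

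- **Condensed article.** The full protocol may code the indicators and add person-level terms. The article never says that categorical variables enter alone. This carries limited weight, because the article does not leave centring open: it states the rule and confines it to continuous variables. An analyst who follows it would leave the indicators uncentred.
- **Examples only.** The two moderators are examples. A continuous moderator such as the stress score would be centred as promised. The activity categories are ordered and could be scored numerically. This stands in part: location is nominal, and the article does not say that activity will be scored.
- **Model not fully given.** The daily outcome and the exact terms are not set out, so the percentages above illustrate the size and do not predict it. This stands.
- **Randomisation protects the interaction.** It does, for between-person differences common to both arms and with similar exposure in both. This stands, and it limits the concern considerably.

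A reader might infer that stable differences, such as employed against not employed, are read as moderation of the intervention. The algebra and the simulation do not support that; such differences cancel unless the intervention effect itself differs by share of days. A reader might also infer false-positive rates near 35%. That figure needs half the reports missing, the lowest assumed ICC, a wide spread of exposure and a 1 SD between-person interaction, all together. Nor do the documents show that low completion or many never-exposed participants are likely. They give only the possible range of 0 to 28 reports, plan push reminders for the daily report, and describe self-monitoring as feasible in earlier piloting.

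**Conclusion.** The point holds as a mismatch between a stated aim and the rule meant to serve it. For categorical day-level moderators, including both examples, the main effect of the day indicator is not purely within-person. The product with group is purely within-person only if the intervention effect does not vary with a person's share of such days.

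The size is small at good adherence. With 28 reports the estimate is about 88 to 99.7% within-person across the assumptions tried, so it would overstate the case to say that the within-person effect is not estimated at all. The share falls to about 80% at worst with 14 reports. These figures rest on an assumed ICC, assumed exposure spread and a random-intercept model, none of which the article gives. The analysis is a secondary moderator analysis. The K6 comparison by telephone interview and the test of general effectiveness are untouched. Severity: minor.

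**What to change.** In the paragraph on conditional effectiveness, replace the reference to continuous day-level variables with: all day-level variables, including the 0/1 indicators of categorical ones. Add that each person's share of such days, and its product with group, enter as separate between-person terms. The within-person product then answers the conditional question, and the between-person product is reported as differential effectiveness.

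The cost is two extra terms per indicator: two for work day against other days, or 4 × 2 = 8 if all five locations are kept. Precision falls slightly, with the standard error multiplied by 1/√(1 − w): 1.007 at w = 1.5%, 1.05 at 10.1% and 1.10 at 17.8%. Trial Status describes the trial as in preparation, so the wording can be changed before any data exist.

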#### Sample Size Calculation

A power analysis was performed to detect a group difference on the primary outcome at post-assessment group. The calculation is based on the assumption that a difference between the supported monitoring group and either AA group or control group within the margin −0.25 < Cohen’s *d* < 0.25 can be neglected. We assume no difference between the two latter groups. Therefore, a between-group difference of *d* = 0.25 should reach statistical significance as an indicator of the general effectiveness of the intervention. The target sample size was computed using Gpower (40) for a repeated-measures analysis of variance for a within-between interaction of time and group (ANOVA). We used a targeted power of 95%, a significance level alpha of 0.05, four assessment waves, a conservative estimate of correlation between measurements (*r* = 65) and variances of the differences between groups (non-sphericity correction epsilon = 0.8). This results in a total *N* = 141. Adding 20% drop-out at T2 and T3, we will include 186 participants (62 per group).

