#### Primary Outcome

*Mental health*: we will use the extent of psychological distress as a measure of mental health. Psychological distress relates to unspecific behavioral, emotional, cognitive, and psychophysiological components of mental health. The Kessler K6 screening scale will be used (33). The K6 has been extensively used in the World Mental Health Survey and has been validated and translated to German. It consists of six items for the measurement of distress during the past 30 days, resulting in a total score ranging between 0 and 24 points. K6 respondents can be classified into three severity groups, with 0–4 points indicating no distress, 4–12 points moderate distress, and 13–24 points high distress (32).

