*Daily life data*: we will compute Cox proportional hazards models to investigate daily life behavior as risk and protective factors of mental health. Cox proportional hazards models are a type of survival model that allows for the estimation of the hazard (or risk) of an event of interest given prognostic variables. We will model changes in mental health as measured by K6 as the outcome event (i.e., improved, maintained, and deteriorated), and separate models will be computed for well-being, intentions to seek help, and help-seeking behavior as outcome event. As risk and protective factors, we will include daily life measures. Risk factors include alcohol and substance use, the frequency of daily hassles, low social activity, and low physical activity. Protective factors include coping behavior, social support, and physical activity. Furthermore, the instability or variability of daily symptoms over the 30-day monitoring period will also be examined as a risk factor by computing within-person variances, first-order autocorrelation, the mean square successive differences, and the probability of acute change according to Jahng et al. (109). Discrimination ability (the ability of the model to separate individuals who develop the event from those who do not) will be assessed with the C statistic. Model calibration, that measure how accurately model predictions match overall observed event rates, will be evaluated with a version of the goodness of fit (110). Internal model validation will be carried out. For all daily life analysis, data from the AA group will be used (*N* = 62).

*Access*: we will describe access to the intervention in terms of population characteristics (sample representativeness), demographics, clinical characteristics, and sample comorbidities using the appropriate descriptive statistics.

*Engagement*: to assess participant engagement, we will examine the proportion of study drop-outs and the proportion of enrolled individuals who respond to the outcome assessments at each time point, and the proportion of daily life assessments filled out during the 30-day interval.

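### The daily-life risk-factor models reduce K6 change to three classes in 62 participants; depending on a cut that the plan does not state, this costs roughly 10 to 40 points of power

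*Protocol article*

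**What the plan says.** The paragraph on daily life data under Statistical Analysis in the protocol article names the method: "we will compute Cox proportional hazards models to investigate daily life behavior as risk and protective factors of mental health". It then defines the outcome: "We will model changes in mental health as measured by K6 as the outcome event (i.e., improved, maintained, and deteriorated". The same event form is carried to other outcomes: "separate models will be computed for well-being, intentions to seek help, and help-seeking behavior as outcome event". The sample is one arm: "For all daily life analysis, data from the AA group will be used", given there as N = 62. Discrimination is to be judged by the C statistic and calibration against event rates, followed by internal validation.

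Under Primary Outcome, the K6 has six items, "resulting in a total score ranging between 0 and 24 points". Under Secondary Outcomes, well-being is a 0-100 rating, help-seeking intention is rated on a 7-point scale, and help-seeking behavior is scored 0 or 1.

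The only rule in the article for classing individual change stands under Treatment response: "Participants with an RCI greater than 1.96 will be classified as “responders,” and those with an RCI below −1.96 will be classified as “deteriorated". The daily-life paragraph does not refer to it.

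**The concern.** The K6 change is collected on a fine scale and then reduced to three labels. Everyone in the maintained class is treated as identical, and so is everyone in each of the other two. With 62 people there is little information to spare. If the cuts are strict, only a few people fall outside the middle class, and any link with alcohol use, hassles, activity, coping or symptom instability has to be found from them.

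The Abstract and the Anticipated Results both present the daily-life factors as an aim of the study. A weak analysis here would probably miss real associations, and a C statistic and calibration based on few events would be unstable. The information lost by classing does not depend on Cox regression as such: a logistic or ordinal model on the same classes would start from the same reduced outcome.

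**Working it through.** **The plan's own figure.** The article states no power or sample size for the daily-life models, so there is nothing to reproduce for them. The only stated calculation is the main one: "We used a targeted power of 95%, a significance level alpha of 0.05, four assessment waves", with d = 0.25, epsilon = 0.8 and a correlation printed as 65 and read here as 0.65. With f = 0.125, three groups and four waves:
- noncentrality = 141 × 0.125² × 4 × 0.8 / (1 − 0.65) = 20.14
- df1 = 2 × 3 × 0.8 = 4.8; df2 = 138 × 3 × 0.8 = 331.2
- power = 0.953. The formula needs 140, which rounds up to 141 for three equal groups.

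The stated total of 141 is therefore confirmed. It concerns the comparison between arms and says nothing about the risk-factor models.

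**Inputs for the daily-life check**
- From the article: n = 62; two-sided alpha 0.05; pre-post correlation 0.65; the RCI limit of 1.96.
- Assumed, because the article gives no value: K6 reliability 0.75 to 0.90; change normal and symmetric around zero; one factor with a correlation of 0.35 with K6 change.

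**Step 1: how many people leave the middle class under the RCI rule.** The RCI divides the change by SD × √(2(1 − reliability)). The SD of the change is SD × √(2(1 − 0.65)). In units of the change SD, the cut is c = 1.96 × √((1 − reliability)/0.35).

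| Reliability | c | Share per tail | People per tail (× 62) |
|---|---|---|---|
| 0.75 | 1.66 | 0.049 | 3.0 |
| 0.80 | 1.48 | 0.069 | 4.3 |
| 0.85 | 1.28 | 0.100 | 6.2 |
| 0.90 | 1.05 | 0.147 | 9.1 |

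**Step 2: how much of the correlation survives.** For symmetric cuts with tail share p, a three-class score of −1, 0, 1 correlates with the underlying change at k = 2φ(c)/√(2p), where φ is the normal density. A factor correlated 0.35 with the change then correlates about 0.35 × k with the classes. Approximate power is Φ(√59 × atanh(0.35k) − 1.96), where 59 = 62 − 3. The simulation column is a check with 20,000 runs at n = 62.

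| Outcome | k | 0.35 × k | Power, formula | Power, simulation | One class versus rest, simulation |
|---|---|---|---|---|---|
| K6 change as a score | 1 | 0.350 | 80% | 81% | – |
| Equal thirds | 0.891 | 0.312 | 70% | 71% | 58% |
| RCI, reliability 0.90 | 0.849 | 0.297 | 65% | 66% | 43% |
| RCI, reliability 0.85 | 0.784 | 0.275 | 58% | 59% | 36% |
| RCI, reliability 0.80 | 0.716 | 0.250 | 50% | 50% | 29% |
| RCI, reliability 0.75 | 0.648 | 0.227 | 43% | 42% | 24% |

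**Step 3: the loss.** Three classes: 81 − 71 = 10 points with equal thirds, and from 81 − 66 = 15 to 81 − 42 = 39 points with the RCI rule. One class against the rest: from 81 − 58 = 23 to 81 − 24 = 57 points.

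**Step 4: sensitivity.** With a weaker factor, correlated 0.25, the formula gives 50% on the score, 41% with equal thirds and 24-38% under the RCI rule. With the planned 20% drop-out, 62 × 0.8 is about 50 people; at correlation 0.35 power is then 71% on the score, 60% with equal thirds and 35-56% under the RCI rule. Power falls for every version, and at correlation 0.35 the loss from classing stays about the same.

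**The case against.** The strongest reply is that the cut has been imported. The RCI rule is written for treatment response and the numbers needed to treat and harm. A reader might infer that it also governs the daily-life models, because the labels are so similar, and conclude that only a handful of people carry the information and that the loss is fixed at the upper end of the range. The article does not say so. Movement between the K6 severity bands is another possible reading. If baseline is spread evenly over the bands, with normal scores and the same 0.65, about 22% would improve and 22% deteriorate, which is roughly 14 people each. The loss would then be about 25 points. Equal thirds lose about 10. This objection stands: the size depends on a cut that may be set in a fuller document.

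A second reply is that these are not power figures for the planned Cox model. That also stands: they come from a one-factor association test and serve to compare codings of the outcome. It does not rescue the classing, because K6 is assessed at a few fixed waves and the article names no event time, so a Cox model has little timing information from which to recover what was lost.

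Third, the work is an addition to the trial, in one arm, and the article sets no power target for it, so no stated figure is contradicted. True, and this limits the weight of the point. The stated interest in detrimental effects gives a reason to report who deteriorates. It is not a reason to make the classes the modelled outcome.

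Finally, no loss has been calculated for well-being or help-seeking intention, and the article gives no classes for them. No size is claimed there.

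**Conclusion.** The point holds as a cheap improvement to a secondary analysis. Classing the K6 change discards information in a sample of 62. For a factor correlated 0.35 with the change, the loss is roughly 10 points of power if the classes are equal thirds, and about 15 to 39 points under RCI ±1.96 with reliability between 0.90 and 0.75. It is larger if a single class is the event. These figures rest on normal symmetric change, a pre-post correlation of 0.65, an assumed reliability and a single factor.

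A reader might go further and infer that the trial's effectiveness result is weakened. The documents do not support this: for effectiveness, outcomes are analysed by repeated-measures analysis of variance, extended with a group factor, and multilevel models are added for moderators. None of these uses the three classes.

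**What to change.** In the daily life data paragraph of Statistical Analysis:
- Replace the Cox model for K6 by a linear or mixed regression of the K6 score, adjusted for baseline K6. Changing the outcome definition alone would not work, since a Cox model cannot take a score at a fixed assessment as its outcome.
- Analyse the 0-100 well-being score and the help-seeking-intention rating as scores in the same way.
- Keep a binary model only for help-seeking behavior, which is recorded as 0 or 1.
- Report improved, maintained and deteriorated as description, and state the cut used.

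The cost is a rewritten paragraph. For the score outcomes, the C statistic and the calibration against event rates give way to explained variance or prediction error and to calibration of predicted scores. No additional data are needed, and the article describes the trial as still in preparation.

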## Abstract

Mobile health (mHealth) could be widely used in the population to improve access to psychological treatment. In this paper, we describe the development of a mHealth intervention on the basis of supportive self-monitoring and describe the protocol for a randomized controlled trial to evaluate its effectiveness among smartphone users with psychological distress. Based on power analysis, a representative quota sample of *N* = 186 smartphone users will be recruited, with an over-sampling of persons with moderate to high distress. Over a 4-week period, the intervention will be compared to a self-monitoring without intervention group and a passive control group. Telephone interviews will be conducted at baseline, post-intervention (4 weeks), and 12-week follow-up to assess study outcomes. The primary outcome will be improvement of mental health. Secondary outcomes will include well-being, intentions toward help-seeking and help-seeking behavior, user activation, attitudes toward mental-health services, perceived stigmatization, smartphone app quality, user satisfaction, engagement, and adherence with the intervention. Additionally, data from the user’s daily life as collected during self-monitoring will be used to investigate risk and protective factors of mental health in real-world settings. Therefore, this study will allow us to demonstrate the effectiveness of a smartphone application as a widely accessible and low-cost intervention to improve mental health on a population level. It also allows to identify new assessment approaches in the field of psychiatric epidemiology.

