### Outcomes

Study outcomes are assessed at four time points: screening (T0), baseline (T1), post-assessment (T3) and follow-up (T4). While the screening (T0) relies on self-assessments collected during participant registration on the study website, structured telephone interviews are conducted at T1, T2, and T3 to assess the primary outcome. The telephone interviews will be conducted by the Academic Survey Lab at the University of Hamburg. Trained interviewers who are blinded to the study condition will conduct the interviews, resulting in an independent outcome assessment to avoid confounding with the self-monitoring data. The secondary outcomes will be self-assessed on the smartphone for all three groups.

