*Engagement*: the extent to which participants are exposed to the intervention and engage with it will be measured by usage metrics of the smartphone application. This includes a date and time-stamped log of when participants open the application and the length of each session. From this information, the number of and length of user interactions with the application will be computed for the 30-day monitoring period. In the intervention group, the users’ engagement with the supportive feedback content will be assessed by tracking the number of received feedback and user ratings of each feedback message (dismiss/remind).

*Adherence*: adherence with outcome assessments will be measured, and in the groups that use self-monitoring, adherence with self-monitoring will be measured. The number of completed daily self-monitoring will be assessed as defined by completion of the last page of an assessment and can range between 0 and 28.

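### Cox models are named for the daily-life analysis, but none of its outcomes has an individual event time

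*Protocol article*

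**What the plan says.** The Daily life data paragraph of the Statistical Analysis section states that "we will compute Cox proportional hazards models to investigate daily life behavior as risk and protective factors of mental health". For the main outcome it says: "We will model changes in mental health as measured by K6 as the outcome event (i.e., improved, maintained, and deteriorated". It adds that "separate models will be computed for well-being, intentions to seek help, and help-seeking behavior as outcome event". Discrimination is to be judged by the C statistic, and the analysis set is the AA group (self-monitoring without support), N = 62.

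The outcomes are described elsewhere in the article:

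- Timing: the Abstract says "Telephone interviews will be conducted at baseline, post-intervention (4 weeks), and 12-week follow-up to assess study outcomes", and the Outcomes section says "structured telephone interviews are conducted at T1, T2, and T3 to assess the primary outcome". (Outcomes also labels post-assessment T3 and follow-up T4. I read T2 as 4 weeks and T3 as 12 weeks.)
- K6 (Primary Outcome): "It consists of six items for the measurement of distress during the past 30 days", scored 0 to 24.
- Well-being, intentions and help-seeking behavior (Secondary Outcomes): respectively a 0-100 rating, a 7-point rating, and a yes/no answer about the past 4 weeks.

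The daily smartphone reports enter the models as risk and protective factors. They are not used to date an outcome.

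**The concern.** A Cox model needs two things for each person: an indicator of whether a defined event occurred, and the time at which it occurred or observation ended. The article's own schedule supplies no such time for any of the four outcomes, and three of the four are not event indicators as described. Whoever runs the analysis must therefore invent an event and a time before a Cox model can be fitted. The output would be labelled a hazard ratio although no rate of occurrence over time was observed. Finding risk and protective factors in daily life is a declared purpose of the study (Abstract, Anticipated Results), so the label matters for how those results are read.

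**Working it through.** **1. The plan's own figure.** The only number attached to this analysis is N = 62, and it reproduces: 186 / 3 = 62. No event rate, hazard ratio or event count is stated, so there is nothing further to reproduce.

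**2. Each outcome against what a Cox model needs.**

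| Outcome | Form as measured | Event indicator? | Time of event? |
|---|---|---|---|
| K6 change | improved / maintained / deteriorated | No: three levels, and *maintained* is the absence of change | No: fixed interviews, 30-day recall |
| Well-being | 0-100 rating | No | No |
| Help-seeking intentions | 7-point rating | No | No |
| Help-seeking behavior | yes/no | Yes | No: undated within 4 weeks |

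Interview dates may vary by some days around the schedule, but that reflects scheduling and not onset. At 4 weeks, the 30-day K6 recall also covers the whole 28-day monitoring period, so a change cannot be placed before or after a given day's report.

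**3. What a Cox fit returns when all times are equal.** This is a simulation. Its assumptions are mine, not the article's: one standard normal predictor, a log odds ratio of 0.7 per SD, about 28% with the event, and every time set to day 28.

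| Fit | n = 62 (17 events) | n = 20,000 (5,661 events) |
|---|---|---|
| Cox, Breslow ties | 0.697 (SE 0.287) | 0.449 |
| Poisson regression on yes/no | 0.697 (SE 0.287) | 0.449 |
| Cox, Efron ties | 0.874 | 0.547 |
| Logistic regression | 1.168 | 0.685 |

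With Breslow ties the Cox coefficient is exactly the Poisson coefficient for the yes/no outcome, that is, a log risk ratio. With Efron ties the same data give another value. At n = 62 the reported ratio would be exp(0.697) = 2.01 or exp(0.874) = 2.40, depending only on a software setting. The gap remains at n = 20,000 (exp(0.449) = 1.57 against exp(0.547) = 1.73), so it is not sampling noise.

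**4. The C statistic.** A survival C compares pairs in which one person's event time is strictly earlier than the other person's time. With one common time the count of such pairs is 0. If non-events tied at that time are instead treated as lasting longer, the statistic becomes the ordinary binary C.

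**5. Illustrative event counts.** These assume that all factors enter one model and that event rates are as shown; the article states neither. With 20% drop-out, 62 × 0.8 = 49.6, about 50. If 10-20% deteriorate, 50 to 62 people give 5 to 12 events. Eight named factors plus four instability indices (for one symptom) make 12 predictors: 5/12 = 0.4 to 12/12 = 1.0 events per predictor. If 50% had the event, 25/12 = 2.1 to 31/12 = 2.6.

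**The case against.** Several points on the other side stand and limit the conclusion.

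- **The estimates are not meaningless.** With one common time and Breslow ties, the fit is a risk-ratio model under the wrong name. The paragraph itself speaks of hazard or risk, and it describes the C statistic and calibration in event/no-event terms. This reads as an intention to model a binary outcome.
- **Two visits give some timing.** Events by week 4 and between weeks 4 and 12 fall into two ordered intervals. A discrete-time or interval-censored model would be possible for a defined binary event. The article specifies none, and it would not suit the rating scales.
- **Definitions may exist.** Treatment response, in the same section, classes responders and deteriorated participants by a Reliable Change Index beyond ±1.96, although Daily life data does not refer to it. Thresholds for the other scales may stand in the full plan, and I do not count their absence as a fault. Thresholds would supply an event but still no event time.

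A reader might infer more than the article supports:

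- **That the question cannot be answered.** Only the Cox analysis as named is unsuitable; the same data suit regression at fixed occasions.
- **That the models are overfitted.** The counts in step 5 of the working rest on assumed rates and on a single joint model. *Improved* is also a named outcome, moderate-to-high distress is oversampled, and internal validation is already planned.
- **That physical activity, listed both as a risk factor (low) and as a protective factor, makes the model collinear.** The item has four categories, and nothing says that both variables enter one model.

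**Conclusion.** The named model does not fit the outcomes. This follows from the article's own schedule and measures and needs no assumed figure. Three of the four outcomes cannot be an event indicator as described. For any binary event, all times are tied at one or two visits, so the estimate depends on tie handling, holds at most two-interval timing, and should not be reported as a hazard ratio. The size of the tie effect (2.01 against 2.40 at n = 62) is illustrative and rests on the simulation's assumptions.

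The scope is limited to the secondary, observational analysis in one arm of 62. The randomized K6 comparison is unaffected.

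A separate, minor point in the same section: completion is described as "the proportion of daily life assessments filled out during the 30-day interval", while completed reports "can range between 0 and 28". If the proportion is literally divided by 30, a participant with no missed day scores 28/30 = 93%. This has no bearing on the choice of model.

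**What to change.** In Daily life data, replace the Cox models as follows:

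- **K6, well-being and intentions:** linear regression of the follow-up score (4 weeks, and 12 weeks) on person-level summaries of the daily measures, adjusted for the baseline score.
- **Help-seeking behavior:** logistic regression.
- **K6 change categories, if kept:** ordinal logistic regression.
- **Discrimination:** the ordinary C statistic for binary outcomes, used only where the outcome is binary.

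The article already names multilevel models for fixed occasions under Differential effectiveness, so the change agrees with its other methods. When reporting, note that the 4-week K6 recall overlaps the monitoring period and the 12-week one does not.

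The cost is wording. No new data or participants are needed, and the article describes the trial as still in preparation. The downside is that regression coefficients and odds ratios take the place of hazard ratios. Separately, state the monitoring period as 28 days throughout.
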